## Abstract

**Background:**

Refugee populations have an increased risk for mental disorders, such as depression, anxiety, and posttraumatic stress disorders. Comorbidity is common. At the same time, refugees face multiple barriers to accessing mental health treatment. Only a minority of them receive adequate help. The planned trial evaluates a low-threshold, transdiagnostic Internet-based treatment. The trial aims at establishing its efficacy and cost-effectiveness compared with no treatment.

**Methods:**

*N* = 131 treatment-seeking Arabic- or Farsi-speaking patients, meeting diagnostic criteria for a depressive, anxiety, and/or posttraumatic stress disorder will be randomized to either the intervention or the waitlist control group. The intervention group receives an Internet-based treatment with weekly written guidance provided by Arabic- or Farsi-speaking professionals. The treatment is based on the Common Elements Treatment Approach (CETA), is tailored to the individual patient, and takes 6–16 weeks. The control group will wait for 3 months and then receive the Internet-based treatment.

**Discussion:**

The planned trial will result in an estimate of the efficacy of a low-threshold and scalable treatment option for the most common mental disorders in refugees.

**Trial registration:**

German Registry for Clinical Trials DRKS00024154. Registered on February 1, 2021.

**Supplementary Information:**

The online version contains supplementary material available at 10.1186/s13063-023-07845-5.

## Administrative information

**Table Taba:** 

Title {1}	Internet-based transdiagnostic treatment for emotional disorders in Arabic- and Farsi-speaking refugees: study protocol of a randomized controlled trial
Trial registration {2a and 2b}	The trial is registered at the German Clinical Trials Registry GCTR: DRKS00024154. The trial was registered on 2021–02-01 and adapted on 2023–11-08
Protocol version {3}	2023–10-23, version 2
Funding {4}	This study is funded by the German Federal Ministry of Education and Research (01EF1806F)

Role of sponsor {5c}	The sponsor co-developed the study design. She will supervise data collection, management, analysis and interpretation, writing of the report, and decision to submit the report. She has ultimate authority over these processes

## Introduction

### Background and rationale {6a}

Mental disorders, such as posttraumatic stress disorder (PTSD), anxiety, depressive, and substance abuse disorders, are common within refugee and migrant populations [1–3]. (Forced) migration, exposure to traumatic events, and post-migration factors all increase the vulnerability to developing mental disorders [1, 4, 5]. At the same time, treatment resources for the specific population of refugees and migrants are very limited in many host countries [6, 7]. Since 2015, approximately 2 million people sought asylum in Germany. Arabic- and Farsi-speaking individuals constitute the largest group among Asylum seekers in Germany in 2022 [8]. The number of psychotherapists in Germany speaking these languages is negligible. In addition, complicated legal regulations make it hard for therapists to get funding for the necessary interpreters. Hence, in Germany, only about 5% of the refugees with mental health problems receive adequate treatment [9]. This is significantly lower than rates in the general population [10]. Language barriers, limited knowledge of treatment options, and perceived stigma further contribute to the large gap between treatment needs and treatment uptake.

Untreated, mental disorders cause major impairments in social and occupational functioning and lead to a loss in quality of life [11]. In refugees and migrants, mental health problems may hinder the process of successfully adapting to the conditions in the host country [12]. Impairment aggravates if more than one mental disorder is present, which is rather the rule than the exception for mental disorders (e.g., [13]). Comorbidity patterns in refugee populations are less well-known than in the general population, but studies suggest that there is substantial comorbidity between PTSD and depression [4] as well as between substance abuse and other mental disorders [14].

It, therefore, seems adamant to invest in low-threshold, accessible interventions that can reach the vulnerable group of refugees and that take into account the comorbid nature of mental disorders.

Internet-based guided self-help interventions can overcome some of the obstacles associated with treatment uptake. They provide a treatment environment that is easy to access, that is less associated with the stigma of mental health treatment, and that is independent of time and location. Numerous studies show that Internet-based guided self-help interventions are effective in the treatment of PTSD, anxiety, and depression [15–17] and demonstrate non-inferiority to face-to-face treatments [18]. Mainly, Internet-based treatments have been investigated in a disorder-specific format, but there are several trials supporting the efficacy of more transdiagnostic approaches [19].

Internet-based treatments also have the potential to overcome language barriers. Treatment contents can be translated into several different languages, and online therapists and clients do not necessarily have to reside in the same area. However, Internet-based interventions for “non-Western” populations are still scarce. In two pilot studies, Kayrouz and colleagues [20, 21] tested the efficacy of an online treatment for depression and anxiety for Arabic-speaking migrants in Australia. The authors reported promising effects for a guided version of the program. In a feasibility study, Lindegaard also reported good effects of a guided program for depression and anxiety for Arabic-speaking patients in Sweden [22]. A small pilot study of a comparable program for *N* = 15 Dari- or Farsi-speaking youths showed high drop-out rates [23]. In two large-scale studies, [name] and colleagues [24, 25] could show that a guided online program led to large changes in PTSD symptoms in patients in war and conflict zones. Although very encouraging, the focus of these trials was on PTSD, excluding other very prevalent problems such as anxiety, depression, and substance abuse. A recent study in Germany evaluated an unguided app as part of a stepped-care approach in Arabic-speaking refugees with depression [26]. The stepped-care approach proved slightly superior compared to treatment as usual. The efficacy of the app, however, was not reported separately.

The majority of refugees access the Internet via smartphones on a daily basis [27]. Developing Internet-based interventions that address the most common mental disorders and that operate on limited therapist time, while, at the same time, providing the necessary clinical support, presents a valuable alternative in situations in which support would otherwise not be available. The aim of the planned trial is therefore to test whether a transdiagnostic, Internet-based treatment is effective in treating emotional disorders in Arabic- and Farsi-speaking refugees.

For the planned trial, we will apply the Common Elements Treatment Approach [28]. CETA is a transdiagnostic, tailored intervention addressing symptoms of depressive and anxiety disorders, PTSD, and substance abuse. CETA was evaluated as a face-to-face treatment in three large RCTs in samples of Burmese refugees [29], survivors of torture and militant attacks in Iraq [30], and couples experiencing alcohol misuse and partner violence in Zambia [31]. CETA demonstrated large effects on post-traumatic stress symptoms, depression, anxiety, substance use, functional impairment, and aggression [29–32]. We adapted treatment contents to the target population of refugees residing in Germany. We followed the conceptual framework and reporting guidelines for cultural adaptation of interventions for common mental disorders [33]. The adaptation process, including expert interviews and focus groups, showed that the CETA manual seemed culture sensitive to the target population, and only surface adaptations were made [34].

### Objectives {7}

In the planned trial, we will test whether a guided, Internet-based version of CETA (CETA-I) is effective compared to no treatment, using a waitlist control condition (WL). We hypothesize that the Internet-based treatment will decrease mental distress, as well as symptoms of anxiety, depression, and post-traumatic stress. We will also investigate potential predictors and mediators. As therapy modules will be differently assigned to patients depending on their primary symptoms, we will specifically focus on baseline symptoms as moderators of the treatment effect. We will additionally explore potential mediators for the relation of treatment and outcome, such as working alliance or CBT skills acquisition. We will also examine cost-effectiveness.

### Trial design {8}

The planned trial applies a randomized controlled design, testing the superiority of an intervention condition (CETA-I) compared to waitlist control.

## Methods: participants, interventions, and outcomes

### Study setting {9}

The randomized controlled trial (RCT) will be realized within an alliance of related subprojects. One of the subprojects focused on adapting CETA to the target population (see item 6a), one focused on translating and evaluating measures of psychopathology for the population, and one evaluated an unguided version of the transdiagnostic online treatment in an inpatient setting.

The trial will take place in Germany.

### Eligibility criteria {10}

We will apply a two-step screening procedure. First, participants will be invited to complete online questionnaires, including the Hopkins Symptom Checklist-25 (HSCL, [35] and the PTSD Checklist for DSM-5 (PCL-5, [36]). Participants scoring above the cutoff on the anxiety and/or depression subscale of the HSCL (> 1.75, [37]) and/or above the cutoff on the PCL-5 (> = [38]) will be invited to take part in a telephone-administered clinical interview. Trained and supervised Arabic- and Farsi-speaking interviewers will administer the Mini-DIPS, a brief, adapted, open-access version of the Anxiety and Related Disorders Interview Schedule (ADIS) based on DSM-5 [39] plus the more elaborate PTSD section of the DIPS [40]. As there are no Arabic or Farsi versions available, we will use our own translations of the Mini-DIPS, realized according to the WHO standards [41].

Inclusion criteria are as follows: (a) age ≥ 18 years; (b) Internet access; (c) primary diagnosis of a depressive disorder (major depressive disorder, persistent depressive disorder), anxiety disorder (generalized anxiety disorder, panic disorder, agoraphobia, social anxiety disorder), or PTSD according to DSM-5; (d) no current psychotic or bipolar disorder; (e) no severe substance use disorder (AUDIT score ≤ 15 for men, ≤ 13 for women; DUDIT score ≤ 25); (f) no serious suicidal ideation at baseline and no suicide attempt within the last 12 months; and (g) no ongoing psychotherapy or unstable psychotropic medication 3 months prior to the study.

### Who will take informed consent? {26a}

A study website will inform about the intervention and the goal and design of the study. Potential participants will be invited to download the study app. Within the app, participants will receive detailed information (see item 32) and will be asked to provide informed consent online.

### Additional consent provisions for collection and use of participant data and biological specimens {26b}

Within the registration process, participants will be asked whether they agree to be contacted for another ancillary study concerning dropout in interventions for refugees. If they agree and drop out of treatment, they will be contacted and will then receive detailed information and be asked to provide informed consent via postal mail.

### Interventions

#### Explanation for the choice of comparators {6b}

A transdiagnostic, cognitive-behavioral Internet-based intervention (CETA-I) will be compared to a waitlist control condition. Comparisons to waitlists are ethical and necessary to establish the efficacy of a new intervention.

#### Intervention description {11a}

The treatment is based on a version of CETA [28] that has been adapted to the context of Arabic- and Farsi-speaking refugees in Germany [34]. CETA includes several modules that are tailored to the patient’s needs. Table 1 gives an overview of the CETA modules applied in the current trial (for a detailed description, please see [28]). Modules differ regarding the number of sessions they encompass.

**Table 1 Tab1:** CETA modules and dosing limits

***Module***	*Target*	*Sessions*
**Psychoeducation and engagement**	Treatment motivation and barriers	1–1.5
**Cognitive restructuring 1**	Dysfunctional cognitive patterns	1–1.5
**Cognitive restructuring 2**	Dysfunctional cognitive patterns	1.5–3.5
**Imaginal and in vivo exposure**	Avoidance/intense fears of specific situations/external and internal cues	2–4
**Behavioral activation**	Low drive, social withdrawal, anhedonia	2–4
**Trauma exposure**	Posttraumatic symptoms	3–5
**CBT for substance abuse**	Problematic alcohol/drug use or gambling	2–4
**Problem-solving**	Addressing real-life solvable problems and problems with treatment engagement	1–3
**Safety planning**	Suicidal ideation, aggression, & violence	1–3
**Finishing steps**	Relapse prevention	0.5–1

## Adaptations to the original CETA manual

For the current trial, we made the following adaptations to the CETA manual. In the two cognitive restructuring modules, we excluded two skills (providing facts and logical questioning). We also decided to start every first cognitive restructuring two sessions with the friend/family role-play skill. For the exposure module, we defined three different types of exposure (imaginative exposure, in vivo exposure, and interoceptive exposure) and will tailor these to the patients. Furthermore, we opened the substance abuse module for patients reporting gambling problems. In the problem-solving module, we specifically probe for problems related to postmigration stressors like discrimination.

## Tailoring

All participants receive the psychoeducation and engagement module, the cognitive restructuring modules, and the finishing steps module. In addition, as follows:Participants scoring above the cutoff on the PCL-5 (> = 33) and/or fulfilling diagnostic criteria for PTSD qualify for the trauma exposure module.Participants scoring above the cutoff of the depression subscale of the HSCL-25 (> 1.75) and/or fulfilling diagnostic criteria for a depressive disorder qualify for the behavioral activation module.Participants scoring above the cutoff of the anxiety subscale of the HSCL-25 (> 1.75) and/or fulfilling diagnostic criteria for an anxiety disorder qualify for the exposure module.Participants indicating mild to moderate addiction problems by scoring x ≤ 13 or more for women and x ≤ 15 or more for men on the AUDIT and 3 ≤ x ≤ 25 for women and 6 ≤ x ≤ 25 for men on the DUDIT, or indicating addictive behaviors on screening for behavioral addictions, and/or fulfilling diagnostic criteria for a mild to moderate substance-related or addictive disorder qualify for the substance abuse module.Participants endorsing a single question asking whether they are facing a major problem in their daily life that has not yet been addressed in therapy and participants who indicate that there is some problem compromising their adherence to therapy qualify for the problem-solving module.Participants who (a) indicate (mild) suicidal ideation on the HSCL-25 during the diagnostic interview, and/or (b) participants who report being a potential threat to others, and/or (c) participants who report being exposed to domestic violence (both (b) and (c) assessed by a single question, rated on a 4-point Likert scale), qualify for the safety module.

In a clinical case conference, a sequence of modules is defined for every patient before treatment, integrating information from the diagnostic interview, baseline questionnaire data, and the patient’s description of his/her main problem. Standard flows for specific (combinations of) diagnoses are referred to (see Appendix 1). A maximum of two types of disorder-specific modules will be administered. Depending on the individual symptom profile, participants receive 5–10 modules.

During treatment, dosage and sequence of modules can also be adapted to the patient’s progress. However, we only allow for specific adaptions. Only modules on safety planning, problem-solving, and substance use can be added when related issues arise. Furthermore, a maximum number of sessions per module is pre-defined (see Appendix 1). Participants will receive a minimum total of 6 sessions and a maximum total of 16 sessions.

Participants can access the online program as an app on their smartphone/tablet and/or as a browser-based version on their desktop computer. Participants are asked to complete one session per week. In each session, participants receive psychoeducation and complete exercises. They receive short written feedback from an online therapist within 48 h after completing a session. Online therapists are trained and supervised Arabic- or Farsi-speaking professionals (bachelor’s or master’s degree in psychology or related subjects). A 2-day training workshop will include training in (a) administering the CETA components; (b) handling the online platform; (c) providing brief, constructive feedback; and (d) enabling crisis management. Supervision will be provided on a biweekly basis.

### Supervision

Supervisors and trainers will be licensed CBT therapists or M.Sc. psychologists in advanced CBT training. Training and supervision in this trial deviate from the standard amount of training in previous CETA trials. First, the amount of training for therapists is lower than in previous trials (2 days instead of 10 days). Second, the supervisors and trainers in our trial are not certified CETA trainers/supervisors. While our trainers and supervisors have received extensive training in providing CETA training and supervision by the authors of CETA ([name] & [name]), they did not complete all the requirements to qualify as certified CETA trainers/supervisors due to time restraints within the study.

#### Criteria for discontinuing or modifying allocated interventions {11b}

A participant may withdraw from the study at any time, for any reason, specified or unspecified, and without penalty or loss of benefits. Furthermore, the principal investigator has the right to discontinue the treatment of participants in case of the following: (a) adverse events (e.g., suicide attempt, severe major depression) that impede treatment or impair the interpretability of the study results or (b) reasons precluding attendance of scheduled treatment modules. Date of discontinuation, all recorded results at that time, and, if known, the reasons for discontinuation will be documented. All participants will be followed up at each assessment point after discontinuation according to the intention-to-treat principle.

We will not allow for the modification of allocated interventions.

#### Strategies to improve adherence to interventions {11c}

## Therapists

Online therapists will receive biweekly supervision. Adherence will further be supported by pre-written feedback messages that online therapists adapt to the individual patient. Adherence will be assessed by analyzing a random selection of written feedback messages. Messages will be analyzed in a qualitative content approach, based on previous work on therapist behavior in guided Internet-based interventions (e.g., [42]). The amount of non-adherent therapist behavior will be assessed.

## Participants

Participants who indicate that there is some problem compromising their adherence to therapy will receive the problem-solving module and work with their therapist to overcome these obstacles.

### Relevant concomitant care permitted or prohibited during the trial {11d}

Participants can continue their respective pharmacological treatment but are requested to not change the dosage or take up additional psychological treatment throughout the treatment/waitlist period.

#### Provisions for posttrial care {30}

Participants in the waitlist control condition receive access to the Internet-based treatment after a waiting period of 3 months.

#### Outcomes {12}

Patient outcome measures consist of self-report questionnaires, which are assessed at baseline (week 0), at week 1, at mid-treatment (week 5), at post-treatment (last session/week 12), and, for the active condition, at 3-month (week 24) and 6-month follow-up (week 36). The primary endpoint is at post-treatment (12 weeks after randomization for the waitlist group).

All questionnaires will be presented via the platform that also hosts the CETA-I intervention. See Table 2 and the section “Data collection and management” for details of measurements at all time points.

**Table 2 Tab2:** Schedule of enrolment, interventions, and assessments

		**Enrolment**	**Allocation**	**Post-allocation**				
**Assessment/activity**		**Baseline**		**Week 1**	**Week 5**	**Post**	**3-month follow-up**	**6-month follow-up**
**Enrolment**	Eligibility screen	x						
	Informed consent	x						
	Allocation		x					
**Intervention**	CETA-I							
	Waitlist							
**Questionnaires for patients**	Sociodemographics	X						
	Healthcare utilization (FIMA & FIMPsy)	X				X		X
	Mental distress, anxiety, depression (HSCL-25)	X			X	X	X	X
	Posttraumatic stress symptoms (PCL-5)	X			X	X	X	X
	Alcohol use (AUDIT)	X			X	X	X	X
	Drug use (DUDIT)	X			X	X	X	X
	Behavioral addictions (own instrument)	X			X	X	X	X
	Health-related quality of life (EQ-5D-5L)	X				X	X	X
	Social support (OSSS-3)	X				X	X	X
	Self-efficacy (GSE)	X				X	X	X
	CBT skills (CBT-SQ)	X				X		
	Outcome expectations (three items)			X				
	Postmigration living difficulties (PMLD-short version)			X				
	Working alliance (WAI-I)				X	X		
	Treatment satisfaction (CSQ-I)					X		
	Negative Effects Questionnaire (NEQ)					X		

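### The primary assessment is dated for the waitlist only; on the natural reading CETA-I is measured at the last session (about week 6 to 16), so the two arms are compared at different times since randomisation

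*Protocol article*

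**What the plan says.** Outcomes {12} places the post assessment and the follow-ups "at post-treatment (last session/week 12), and, for the active condition, at 3-month (week 24) and 6-month follow-up (week 36", and then says: "The primary endpoint is at post-treatment (12 weeks after randomization for the waitlist group". The 12-week clock is thus attached explicitly to one arm.

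The abstract says that the treatment "is tailored to the individual patient, and takes 6–16 weeks". The Tailoring section gives the session count: "Participants will receive a minimum total of 6 sessions and a maximum total of 16 sessions". It also gives the pace: "Participants are asked to complete one session per week". Length varies by patient: "Depending on the individual symptom profile, participants receive 5–10 modules". The same section allows dosage and sequence to change with progress.

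Statistical methods {20a} compares the post-assessment HSCL-25 total between arms by baseline-adjusted regression and names no term for assessment time. On discontinuation, section {11b} says: "All participants will be followed up at each assessment point after discontinuation according to the intention-to-treat principle". Table 2 schedules the HSCL-25 at baseline, week 5, post and the two follow-ups. The weekly measures are shorter instruments (PHQ-4 and a short PCL-5).

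**The concern.** A randomised comparison is protected when both arms are measured on the same clock. Here the waitlist is measured at week 12, while CETA-I, read naturally, is measured when each course ends. Four things follow.

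- **Estimate.** Participants enter by scoring above symptom cut-offs, so some untreated improvement and regression to the mean is plausible. If the arms have had different lengths of time for it, the difference enters the treatment contrast. Adjusting for the baseline score does not remove it.
- **Link to severity and adherence.** In CETA-I only, the measurement date depends on symptom profile, progress and pace. Baseline symptoms are also the stated moderators of interest, so those interactions are mixed with timing.
- **Early stoppers.** Someone who leaves treatment has no regular last session. The plan wants them assessed but does not make clear when, and the multiple imputation then targets a value at an unclear time.
- **Follow-ups.** Weeks 24 and 36 are 3 and 6 months after post only if post is at week 12.

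An analysis plan could not repair this afterwards. A participant who finishes at week 8 would have no HSCL-25 near week 12, because the next one is due at the 3-month follow-up.

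**Working it through.** **1. The plan's own figure.** Sample size {14} gives 44 per arm for d = 0.6, two-sided 5%, 80% power.

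- n = 2 × (1.960 + 0.842)² / 0.6² = 43.6, so 44. Power with 44 per arm is 80.4% at d = 0.6 and 96.3% at d = 0.8. This reproduces.
- Attrition of 40% and 20%: 44/0.6 = 73.3 (74) and 44/0.8 = 55, total 129 against the stated 131. Starting from the t-test value of 44.6 (45), 45/0.6 = 75 and 45/0.8 = 56.25, which matches the stated 75 and 56.

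The sample size is sound and is not affected by this point.

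**2. Range of individual offsets.** At one session per week, 6 to 16 sessions put the last session at about week 6 to week 16. Against waitlist week 12 the offset is 6 − 12 = −6 weeks to 16 − 12 = +4 weeks. The pace is requested, not enforced, so week 16 is not a firm limit.

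**3. Where the arm's mean might lie.** Sessions from Table 1:

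- Modules given to everyone: minimum 1 + 1 + 1.5 + 0.5 = 4; maximum 1.5 + 1.5 + 3.5 + 1 = 7.5.
- Plus one disorder-specific module (2–4, or 3–5 for trauma): 4 + 2 = 6 to 7.5 + 5 = 12.5; midpoint 9.25.
- Plus two, the stated maximum: 4 + 2 + 2 = 8 to 7.5 + 5 + 4 = 16.5, capped at 16; midpoint 12.

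This leaves out the optional problem-solving and safety modules and assumes the requested pace. It points to a mean of roughly week 9 to week 13, not to either extreme.

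**4. Bias.** Let W be the mean last-session week in CETA-I and s the untreated improvement in SD per 12 weeks, taken as linear. The document does not give s; 0.1 to 0.4 is assumed.

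Bias in d = s × (W − 12)/12, positive in favour of CETA-I.

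| W | s = 0.1 | s = 0.4 |
|---|---|---|
| 9 | 0.1 × (−3/12) = −0.025 | 0.4 × (−3/12) = −0.10 |
| 12 | 0 | 0 |
| 13 | 0.1 × (1/12) = +0.008 | 0.4 × (1/12) = +0.033 |

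**5. Consequence for power.** With a true d of 0.6 and W = 9, the expected d is 0.575 to 0.50. Power is Φ(d × √22 − 1.960), where √22 = 4.690 for 44 per arm. At 0.575 it is Φ(0.737) = 77%; at 0.50 it is Φ(0.385) = 65%; the planned value is 80%.

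**6. Early stoppers.** The assumed 40% of 75 is 30 CETA-I participants. The article does not separate leaving treatment from missing the assessment, so 30 shows the scale only; it is not a count of undated assessments.

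**7. Follow-up spacing, if post is the last session and weeks 24 and 36 count from randomisation.**

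| Last session | Gap to week 24 | Gap to week 36 |
|---|---|---|
| Week 6 | 18 weeks | 30 weeks |
| Week 12 | 12 weeks | 24 weeks |
| Week 16 | 8 weeks | 20 weeks |

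**The case against.** The wording is not fully explicit. The entry for post names both the last session and week 12 without splitting them by arm, and follow-ups at weeks 24 and 36 fit a nominal week 12 in both arms. Week 12 could also be meant as the fallback date for those who stop. This stands in part: the arm-specific clock is the natural reading, not a certain one. But if week 12 was meant for everyone, the reference to the last session is wrong for anyone who does not finish then. Either way the CETA-I date is not uniquely fixed.

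Measuring at the end of treatment is also a legitimate choice of question, and a common week 12 catches longer courses before completion. That is a real cost and belongs in the description of the estimate. It does not justify measuring the comparator on a different clock, since waitlist assessments are not matched to the treated participants' dates.

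A reader might infer more than the documents support:

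- **That the bias favours CETA-I or inflates false positives.** Early finishing works against CETA-I, and the direction is unknown.
- **That a large share of the planned d is at risk.** Putting the whole arm's mean at week 6 or week 16 gives larger figures, but Table 1 does not point there.
- **That measurement time is set wholly after randomisation.** The initial module sequence rests largely on baseline information; progress, added modules and pace come later.
- **That the case conference pushes the last session beyond week 16.** No delay between randomisation and the first session is stated.
- **That cost exposure differs by a known ratio.** No recall window for FIMA/FIMPsy is given, and the economic analysis is a Markov model that also draws on the literature.

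**Conclusion.** The point holds as a defect in how the primary time point is fixed. The waitlist has a dated assessment. CETA-I, on the natural reading, does not, and its assessment may fall anywhere from about week 6 to week 16. Followed that way, the primary contrast compares arms at different times since randomisation.

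The size is uncertain and probably modest. Under linear untreated improvement of 0.1–0.4 SD per 12 weeks and a mean last session between weeks 9 and 13, the bias in d runs from about −0.10 to +0.03, passing through zero at week 12. As a share of the planned 0.6 that is at most 0.10/0.6 = 17% understated or 0.033/0.6 = 6% overstated. Both the drift and the mean week are assumptions. The unclear date for early stoppers and the ambiguous follow-up spacing do not depend on the drift.

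This does not show that the result will be biased by a given amount. It is an inexpensive correction to make while data can still be collected on the right date.

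**What to change.** - Collect the HSCL-25 in both arms at 12 weeks after randomisation, regardless of treatment status, and name this as the primary between-group comparison. Collect the secondary outcomes, EQ-5D-5L and FIMA/FIMPsy at the same assessment.
- Keep the last-session assessment in CETA-I as a supplementary, within-arm measure.
- State one anchor for weeks 24 and 36 and label them accordingly: either weeks from randomisation, or 3 and 6 months after the last session.
- Describe the primary contrast as the effect at 12 weeks.

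**Cost.** A change to the platform's assessment trigger, amended wording, and one extra questionnaire set for CETA-I participants who do not finish at week 12. Those on longer courses are measured before completion, so the estimate may be smaller than an end-of-treatment one; by how much cannot be worked out from the document. The week-12 date fits the existing 3-month wait. The 44 per arm and the total of 131 are unchanged.
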